### Data monitoring

There will be no Data Monitoring Committee or interim analyses with respect to the study outcome. In order to determine the appropriate point at which to cease recruitment, members of the study team will continuously monitor the acquired sample size including only data from students who provided apparently valid self-generated pseudonyms (i.e., combinations of numbers and letters in the expected sequence).

### Assessment and monitoring of harmful effects

In addition, the intervention development lead will monitor the occurrence of any adverse events that may result in student harm and may need to be managed appropriately. However, we have used the numerous teacher interviews and feasibility tests to anticipate a number of possible adverse events that may occur (i.e., bullying during role-playing or group discussions) and to include guidance on how to appropriately manage these scenarios in our training for interventionists.

### Analysis

The analyses on intervention effects will be conducted on an intention-to-treat basis, including data from all students based on the groups they were randomly assigned to. The main confirmatory analysis pertains to the group difference between intervention and control group in intention to be vape- and smokefree at the 12-month follow-up (T4), adjusted for baseline (T0). All other analyses, including analyses of secondary behavioral outcomes and additional time points, will be considered secondary or exploratory, and no formal multiplicity adjustment will be applied.

Group differences in secondary behavioral endpoints (i.e., prevalence and frequency measures) will be analyzed across all product categories (e.g., prevalence defined by the use of at least one of the products presented in the questionnaire) as well as individually for each product reported by at least 1% of the sample.

For continuous and dichotomous outcomes, we will use generalized mixed effect regression analyses (i.e., linear regression for the outcome of intention to be vape- and smoke-free; logistic regression for [binary] susceptibility, prevalence measures, current vaping/smoking and regular vaping/smoking). The primary analyses will use a two-level structure, with students at Level 1 nested within schools at Level 2, reflecting the school-level randomization and the role of the school as the primary clustering unit. In regard to count data, we will use Generalized Estimating Equations to conduct zero-inflated negative binomial regressions for count outcomes with many zeros, i.e., the 30-day frequency. We will investigate intervention effects using the criterion of statistical significance (*p* < 0.05) of the regression coefficients for the treatment condition variable (adjusting for prespecified baseline covariates; all measured at T0: intention, age, gender, parental vaping/smoking, best friend’s vaping/smoking, objective socioeconomic status, school attachment, self-esteem and distress). All models will be specified with a maximal random effects structure and progressively simplified as needed to reach convergence.

To handle missing data appropriately, we will conduct a comprehensive analysis of attrition patterns, multiple imputation and sensitivity analyses to check the robustness of our inferences to departures from the underlying assumption of missingness at random.

We will initially test the hypothesized mediators of intervention effects in simple mediator models before proceeding with a multiple mediation analysis. All mediation analyses will account for the nesting of students within schools using mixed-effects modelling approaches.

*Program evaluation by social determinants of health.* We will investigate SDOH subgroup differences in absolute levels of risk factors and outcome variables, as well as differential predictive power of those risk factors for intention, susceptibility, and vaping/smoking. Last, we will explore differential intervention effects and mediators by reporting effect sizes by subgroup.

*Further examination of results.* In additional secondary and sensitivity analyses, we will examine alternative modelling strategies that incorporate class-level effects, the use of alternative indicators or variable codings, and longitudinal models based on all available measurement time points. The quantitative analyses described above will be conducted using RStudio and SPSS. Further details of the statistical analysis plan are available in the pre-registration^37^.

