### Analytic sample and sample size

We calculated the sample size needed to detect a difference between intervention and control group at 80% power (*α* = 5%) in accordance with the National Institutes of Health recommendations for the analysis of cluster-randomized trials^78^. Consistent with randomization at the school level, the school was treated as the primary clustering unit in a two level structure (school- and student-level observations).

The following estimates of the relevant factors were derived from previous research: Focusing on our continuous primary outcome variable intention, we conservatively assume an intervention effect size of Cohen’s *d* = 0.2^79^. Based on the current literature, the intraclass correlation (ICC) of this psychosocial variable is expected to be lower than that of overtly visible risk behaviors (e.g., smoking) that may be subject to social mimicry^80^. We therefore used an ICC estimate of 0.005, as reported by Siddiqui et. al^81^ for the intention to smoke in 47 schools. Assuming an average cluster size of 60 students with usable data per school, based on an average of 3–4 classes per school with 22 students per class [^77^], our analysis yields a minimum sample size of 10 schools in each study arm (1,200 students). Expecting an attrition rate of up to 20%^52^, we aim to recruit *N* = 1,500 students in at least 26 schools (see Fig. 2: Anticipated participant flow). Because the ICC assumption is subject to uncertainty and higher ICC values would reduce effective power, we will recruit beyond this minimum target if feasible.

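### The 30-day-frequency model contradicts itself and leaves the deciding treatment coefficient open; the 1% product threshold may also be too low for the full covariate set

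*Protocol article*

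**What the plan says.** All of this stands in the Analysis section of the protocol article unless another section is named.

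- **Count outcome.** For 30-day frequency, "we will use Generalized Estimating Equations to conduct zero-inflated negative binomial regressions for count outcomes with many zeros".
- **Random effects.** The same paragraph says that every model starts from a maximal random effects structure and is simplified until it converges. No exception is made for the GEE.
- **Decision rule.** Effects are judged by p < 0.05 for the treatment regression coefficients (plural), adjusted for nine T0 covariates: intention, age, gender, parental use, best friend's use, objective SES, school attachment, self-esteem and distress.
- **Products.** Prevalence and frequency are analysed across products and also "individually for each product reported by at least 1% of the sample". Neither the measure nor the wave that defines the 1% is given.
- **Status.** Only the T4 comparison of intention is confirmatory. Everything else is secondary or exploratory, and further detail is referred to the pre-registration.

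The Additional measures paragraph of the Measures section presents eight of the nine covariates (all but T0 intention) as covariates for the primary outcome.

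**The concern.** Thirty-day frequency is one of the outcomes named in the trial's hypotheses, so a reader will expect one defined result. The text instead joins three elements that do not form one model: a marginal estimating-equation method, a two-part mixture, and a random effects structure.

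The decision rule is also open. The excess-zero coefficient, the count coefficient and the effect on the overall mean answer different questions, and the text does not choose among them. The count part alone compares students who belong to a latent at-risk group in each arm. If the programme changes who belongs to that group, randomization no longer protects the comparison. With no rule fixed, the choice could be made after the results are seen.

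The product-level threshold is a separate and smaller matter. A percentage of the sample does not guarantee enough events for the model to be fitted, and recent or regular use can be much rarer than lifetime use.

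**Working it through.** **1. The base of 1,200.** Inputs from Analytic sample and sample size: d = 0.2, α = 5% (taken as two-sided), power 80%, ICC 0.005, 60 students per school, attrition 20%.

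- Unclustered n per arm = 2 × (1.96 + 0.8416)² / 0.2² ≈ 393.
- Design effect = 1 + 59 × 0.005 = 1.295; 393 × 1.295 = 509 per arm; 509 / 60 = 8.5 schools by normal quantiles.
- With t quantiles on 18 df: (2.101 + 0.862)² × 2 / 0.04 × 1.295 / 60 = 9.47, so 10 schools per arm and 1,200 students (noncentral-t power 0.821; 0.774 with 9 schools).
- 1,200 / 0.8 = 1,500 to recruit.

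The stated sample size reproduces.

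**2. Two coefficients, two verdicts.** In a zero-inflated model the overall mean is (probability of being at risk) × (mean count if at risk). Assume 12% at risk under control, 6% under intervention, and a mean of 6 in both groups.

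- Overall means: 0.12 × 6 = 0.72 and 0.06 × 6 = 0.36; ratio 0.50.
- Count-part ratio: 6 / 6 = 1.

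The overall effect is a halving, carried entirely by the excess-zero part. In 150 simulated trials of 1,200 students (dispersion 0.8, no covariates, no school effect, all converged), the excess-zero treatment coefficient was significant in 91%, the count coefficient in 5%, and the verdicts differed in 86%. These inputs are assumptions chosen to show the mechanism; the documents give no 30-day figures.

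**3. Users against parameters.** Intercept + treatment + nine covariates = 11 fixed effects, of which 10 are slopes. At the floor, 1% × 1,200 = 12 users (15 of 1,500). Lifetime shares come from Table 1 and the first Discussion section (Grade 6 feasibility sample, with the 3.7% for cigarettes read as that sample's figure):

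| Lifetime use | Share | Users of 1,200 | Users per slope |
|---|---|---|---|
| Threshold floor | 1% | 12 | 1.2 |
| Cigarettes | 3.7% | 44 | 4.4 |
| Disposable e-cigarettes | 6.5% | 78 | 7.8 |
| Hookah | 7.6% | 91 | 9.1 |
| Any product | 11.96% | 144 | 14.4 |

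For regular use, Table 1 reports generally only 1–2 students per grade cohort. As a rough scaling with one Grade 5 cohort per school, 20 to 26 schools give 20 × 1 = 20 to 26 × 2 = 52 regular users over all products, about 2 to 5 per slope.

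**4. What sparse fits do.** Two logistic simulations of the 11-parameter model were run, with assumed covariate effects and no school effect.

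The first had 400 trials per setting and a true OR of 0.50 (log OR −0.693):

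| Events | Failed or separated | Mean log OR | Overstatement |
|---|---|---|---|
| 12 | 16.8% | −0.776 | 12% |
| 24 | 2.0% | −0.748 | 8% |
| 48 | 0.5% | −0.718 | 4% |
| 96 | 0% | −0.694 | 0% |

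At 12 events the estimated OR had a 95% range of 0.09 to 1.68.

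The second had 800 trials per setting. At 1% prevalence, quasi-separation occurred in 11% of fits (true OR 1) and 15% (true OR 0.5), Wald type I error was 0.024, and power for OR 0.5 was 0.14. That power was 0.59 at 3.7%, 0.83 at 6.5% and 0.97 at 11.96%, with separation in at most 0.1% of fits.

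**The case against.** The strongest defence is that none of this touches the confirmatory result. The article labels these analyses secondary or exploratory and points to a pre-registration that may settle the count model. That limits the importance, but the conflict between GEE and random effects for all models is in the article's own text and would remain there.

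A reader might infer that the analyses cannot work as written. The documents do not support that:

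- The decision rule speaks of coefficients in the plural, so it does not demand a single one. What is missing is the rule for combining or choosing.
- Estimating equations can be built into an EM-type fit of a zero-inflated mixture, so GEE with zero inflation is not impossible in principle.
- Most fits at 12 users still converge, and their type I error is below nominal. The harm is instability and lack of information, not false positives.
- Twelve users is the floor. The lifetime figures give 44 to 91 users for the three products reported. Rarer measures remain exposed.
- The 11-parameter model is one reading. The Analysis section can be read as applying the list to every model, but the Measures section ties eight of the nine covariates to the primary outcome.

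Nor should a reader infer faulty GEE standard errors, unsuitable software or a multiplicity error. The article neither states nor rules out a small-sample correction. It does not say which routines will be used. Its no-adjustment policy is openly declared beside a single confirmatory test. A requirement of about 100 users would also go further than the first simulation supports, since 48 events already gave 0.5% failure and about 4% overstatement.

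**Conclusion.** The concern holds in a limited form. The firm part is the 30-day-frequency analysis: the specification is internally inconsistent, and the significance rule leaves open which of at least two treatment effects decides. The 86% disagreement depends on an assumed effect that acts only on whether students use. The existence of two coefficients with no rule between them depends on no assumption.

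The 1% threshold is a conditional weakness. If the full covariate list applies to product-level logistic models, about 12 users may face 11 fixed-effect parameters, with 11–17% of fits failing or separating and power near 0.14 for an OR of 0.5. The simulations omit school effects and assume covariate effects, so these figures are indicative. If the 1% refers to lifetime use, 30-day or regular-use models could have fewer than 12 users.

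Both points deserve correction. Neither affects the confirmatory conclusion on intention.

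**What to change.** **Count outcome.** Name one clustered count model with one overall treatment effect as the test of 30-day frequency. One suitable choice is a negative binomial log-link model with a school random intercept and the T0 value of the outcome, which gives a single rate ratio. Report any zero-inflated model as a sensitivity analysis with both parts shown. Restrict the maximal random effects sentence to the mixed models.

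**Product-level and other sparse binary outcomes.** State which covariates apply to secondary outcomes. Replace the 1% rule by a prespecified number of events in the outcome and wave being modelled; about 50 is supported by the first simulation above. Below that number, give counts by arm with a Firth-penalized model or a reduced model containing treatment and the T0 value.

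**Cost.** Only analysis wording changes, with no change to data collection or sample size. The article already provides for documenting protocol changes through updates of the pre-registration, and this is best done before outcome data are analysed. The small downside is that rare products get fewer covariates or descriptive reporting only.

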### Measures

Table 4 presents a summary of the measurements utilized in the student questionnaires at each assessment time-point. For a comprehensive overview of the measurements employed in the student, teacher, and interventionist surveys, including construct order, number of items, translated example items, and source references, see Supplementary 2, Tables S2–S5. Most constructs are assessed using brief two- to three-item scales, with a small number of single-item measures to reduce respondent burden for the target group. Key proposed mechanisms are measured using well established operationalizations from the Reasoned Action Approach and related research^51^. A small number of measures were drawn from previous studies (see Supplementary 2) based on their psychometric properties. Other scales assessing mechanisms and covariates were developed within the project. In our feasibility sample, internal consistency for all multi-item scales used in the student questionnaire was acceptable (Cronbach’s α = 0.72–0.83).

**Table 4 Tab4:** Summary of measurements used in the student questionnaires.

Measurement	T0	T1^a^	T2	T3	T4	Tn
*Outcomes*						
Intention to be vape- and smoke-free^b^, susceptibility to vaping and smoking	X	X	X	X	X	X
Lifetime prevalence, 12-month and 30-day prevalence, current vaping/smoking, regular vaping/smoking, 30-day frequency	X		X	X	X	X
*Proposed mechanisms / mediators*						
Personal agency: self-efficacy to be vape- and smoke-free, refusal self-efficacy, refusal self-concept	X	X	X	X	X	X
Action planning	X	X	X	X	X	X
Descriptive and injunctive norms towards being vape- and smoke-free	X	X	X	X	X	X
Attitude towards being vape- and smoke-free (direct measure)	X	X	X	X	X	X
Outcome expectations (indirect attitude measure)	X	X	X	X	X	
Stress and problem coping self-efficacy, stress and problem coping planning, affect^a^, anxiety^a^				XX	X	X
*Program evaluation*						
Satisfaction		X	X	X		
Careful responding /attention	X	X	X	X	X	X
*Sociodemographics and covariates*						
Age, gender	X	X	X	X	X	X
SDOH, country of origin, objective SES, subjective SES, ethnicity/racial identity, language, religion, general health	X					
Vaping/smoking of relevant others, parental disapproval of vaping/smoking, accessibility, school attachment, self-esteem, satisfaction with looks, distress	X					

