*Proposed mechanisms (mediators).* As specified in our logic model, the main proposed determinants of behavior and mechanisms of change to be underlying the intervention effects on the primary outcome (intention to be vape- and smoke-free) include self-efficacy to be vape- and smoke-free, refusal self-concept, refusal self-efficacy, action planning, descriptive and injunctive norms towards being vape- and smoke-free, and attitudes towards being vape- and smoke-free (direct measure). For behavioral outcomes (i.e., susceptibility, prevalence, and frequency), intention will be modelled as an additional mediator alongside the mentioned psychosocial determinants (e.g., self-efficacy, refusal self-concept, action planning). In addition to the quantitative assessment of mediators via student questionnaires, the proposed mechanisms of change will be explored qualitatively in semi-structured interviews conducted after the core workshop.

*Additional measures.* The baseline assessment will include a number of sociodemographic variables and proposed determinants of vaping and smoking. Among these, age, gender, objective SES, school attachment, parental vaping/smoking, best friend’s vaping/smoking, self-esteem and distress will serve as covariates in the main analysis of intervention effects on the primary outcome. In addition, we will assess SDOH to examine differential intervention efficacy and underlying mechanisms of action by SDOH subgroup. For the purpose of sensitivity analyses, the student questionnaires will also include different attention screeners (e.g., “Please show us that you are reading the questions carefully and mark response option ‘Definitely’; “How much do you agree? ‘I am currently responding to a questionnaire’) and an item to detect careless responding^88^.

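### The covariate list in the Analysis section gives the susceptibility and use models T0 intention, not each outcome's own T0 value, and its scope conflicts with the Measures section

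*Protocol article*

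**What the plan says.** The Analysis section assigns linear mixed regression to intention, "logistic regression for [binary] susceptibility, prevalence measures, current vaping/smoking and regular vaping/smoking", and a zero-inflated negative binomial model to 30-day frequency. It then gives one covariate list for the treatment coefficient: "adjusting for prespecified baseline covariates; all measured at T0: intention, age, gender, parental vaping/smoking", followed by best friend's use, objective SES, school attachment, self-esteem and distress. The sentence comes after all three model types and names no single outcome. Adjustment for an outcome's own baseline is stated only for the confirmatory contrast, intention at T4.

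Under Additional measures, the Measures section names the same variables without T0 intention and says that they "will serve as covariates in the main analysis of intervention effects on the primary outcome".

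Table 4 marks "susceptibility to vaping and smoking" at T0, and also "Lifetime prevalence, 12-month and 30-day prevalence, current vaping/smoking, regular vaping/smoking, 30-day frequency". Neither is restricted to the intervention arm at T0.

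Under Further examination of results, the Analysis section adds "longitudinal models based on all available measurement time points" among the secondary and sensitivity analyses and refers to the pre-registration for further detail. All analyses other than the confirmatory one "will be considered secondary or exploratory, and no formal multiplicity adjustment will be applied".

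**The concern.** For a repeated measure, the T0 value of the same outcome is normally the most useful covariate. T0 intention has that role for the primary outcome only. Applied as written to the other outcomes, the list adjusts for whether the parents and the best friend vape or smoke, but not for whether the child already does or is already susceptible.

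Susceptibility and use carry directional hypotheses, and reducing initiation and consumption is a stated aim. Leaving out their T0 values gives up precision that the trial has already paid for, and lets more of a chance T0 difference between arms show up as a T4 difference. The unclear scope also leaves the covariate set for these outcomes open to choice later.

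**Working it through.** **1. The plan's own figure.** Inputs from Analytic sample and sample size: d = 0.2, 80% power, 5% alpha (taken as two-sided), ICC 0.005, 60 pupils per school. Without clustering, 393 per arm. Design effect 1 + 59 × 0.005 = 1.295, so 393 × 1.295 = 509 per arm, or 509/60 = 8.5 schools. With a t distribution on 2(k − 1) degrees of freedom, power is 77.4% at k = 9 and 82.1% at k = 10. Ten schools per arm (1,200 pupils) is reproduced, and 1,200/0.8 = 1,500. This concerns intention only. The article gives no sample size for the secondary outcomes.

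**2. Chance T0 difference, 600 per arm.** SE = √(2 × p(1 − p) × DE / 600). The rates come from the Grade 6 feasibility sample and are assumed here for Grade 5. ICC 0.02 (DE = 1 + 59 × 0.02 = 2.18) is an added assumption.

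| T0 measure | p | ICC | SE (points) | 95% range (points) |
|---|---|---|---|---|
| Susceptibility | 0.358 | 0.005 | 3.15 | ±6.2 |
| Susceptibility | 0.358 | 0.02 | 4.09 | ±8.0 |
| Lifetime use | 0.1196 | 0.005 | 2.13 | ±4.2 |
| Lifetime use | 0.1196 | 0.02 | 2.77 | ±5.4 |

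**3. Precision, by algebra.** Let a be the correlation of T0 intention with the T4 outcome, b that of the T0 outcome with the T4 outcome, and c that of the two T0 measures (intention reversed so that all are positive). With both covariates, R² = (a² + b² − 2abc)/(1 − c²); with intention alone, R² = a². The residual variance is multiplied by (1 − R²)/(1 − a²). Example: a = 0.2, b = 0.5, c = 0.4 gives R² = (0.04 + 0.25 − 0.08)/0.84 = 0.25 and a ratio of 0.75/0.96 = 0.78. Over a = 0.2–0.35 and c = 0.4–0.6 (all assumed), the ratio is 0.94–0.99 for b = 0.3, 0.76–0.85 for b = 0.5 and 0.45–0.57 for b = 0.7.

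**4. Precision and carry-over, by simulation.** Setting: 20 schools of 60 pupils, no programme effect, 35.8% susceptible at T0, linear model on the risk-difference scale, 2,000 runs per row. Carry-over is the shift in the T4 contrast, in points, per point of T0 imbalance.

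| T0–T4 correlation | Variance ratio, own baseline added | Carry-over, intention only | Carry-over, own baseline added |
|---|---|---|---|
| 0.29 | 0.87 | 0.37 | 0.17 |
| 0.50 | 0.72 | 0.52 | 0.12 |
| 0.63 | 0.56 | 0.64 | 0.12 |

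The variance therefore falls by 13% to 44%. A 5-point T0 imbalance shifts the T4 contrast by 1.9 to 3.2 points with intention only (5 × 0.37 and 5 × 0.64), and by 0.6 to 0.9 points with the own baseline added (5 × 0.12 and 5 × 0.17). The mean estimate is about zero in every setting.

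**5. Lifetime use.** A T0 ever-user should still be one at T4. With 11.96% at T0 and an assumed 16–30% at T4, the share of T4 ever-users who started before the programme is 0.1196/0.16 = 75% down to 0.1196/0.30 = 40%. Carry-over without the own baseline is (1 − p4)/(1 − p0): 0.84/0.8804 = 0.95 down to 0.70/0.8804 = 0.80.

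**The case against.** The strongest objection is scope. The Measures section ties these covariates to the primary outcome, and the Analysis list opens with that outcome's own baseline. On that reading the article fixes no covariates for the secondary models, and the pre-registration, which is not shown, may do so. This makes the text ambiguous. It does not settle the matter, because the Analysis sentence follows every model type and, taken literally, gives the behavioural models the wrong baseline.

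Several stronger readings are tempting but not supported:

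- A reader might infer that the T0 values enter no stated model. The longitudinal models would use them, though only as secondary or sensitivity analyses.
- A reader might infer bias. Under school randomisation there is none on average. Chance imbalance is part of the sampling error that a correctly clustered standard error covers, so lost precision and carry-over are largely two views of one cost.
- A reader might infer that chance imbalance is as large as the programme effect. The article states no effect for susceptibility. If d = 0.2, stated for intention, is assumed on a latent scale, 35.8% (z = −0.364) moves to 28.6% (z = −0.564), about 7 points. The SE of 3.15 points is less than half of that.

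The size of the gain is also open to challenge, and this stands. All correlations are assumed, and the calculations contain T0 intention but not the other listed covariates, which would absorb part of the gain. The planned models are logistic, where adjustment changes the conditional odds ratio itself, so the variance ratios do not transfer directly to its standard error.

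**Conclusion.** The point holds for the secondary analyses. On the plain reading, the main susceptibility and use models omit the outcome's own T0 value although it is collected in both arms, and the two statements of the covariate set disagree in scope. The cost is precision and partial carry-over of chance imbalance. For susceptibility, the own baseline would cut the variance of the contrast by roughly 13–44% at assumed T0–T4 correlations of about 0.3 to 0.6. The algebra shows a gain of only 1–6% in some settings at a correlation of 0.3. Carry-over is greatest for lifetime use. The confirmatory analysis already adjusts for its own baseline, and neither it nor the sample size is affected. The change is worth making because it needs no new data, but the trial's main conclusion does not depend on it.

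**What to change.** In the Analysis section:

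- State that each secondary outcome's model adjusts for the T0 value of that outcome, in addition to the listed covariates.
- For lifetime use, analyse initiation among T0 never-users instead. T0 ever-users remain ever-users, so T0 status as a covariate would nearly separate the logistic model.
- For rare endpoints (regular use, current use, 30-day frequency), use one broader T0 own-use indicator, such as any lifetime use. The development study reports regular use in only one or two pupils per grade cohort, so matching T0 cells may be almost empty.
- Say which outcomes the list covers, and bring the Additional measures paragraph into line. If the pre-registration already settles this, the article should match it.

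The cost is wording, to be settled before unblinding. It adds one parameter per model, with possible sparse cells for the rare endpoints. The initiation analysis uses a somewhat smaller sample: about 1,056 of 1,200 pupils (1,200 × 0.8804) if T0 lifetime use equals the feasibility figure.
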